**Figure 1. f1:**

Nested prospective cohort study design.

The PRISMA MNH study was approved by the George Washington University’s Committee on Human Research (IRB: FWA00005945) on September 30, 2022 and received local and national ethical approval in Kenya (KEMRI/CGHR/04/10/358/4166; approved September 16, 2022), Zambia (IRB00001131 of IORG0000774; approved April 8, 2022 and UNC Biomedical IRB 356795; approved August 8, 2022), and Pakistan (001-VPT-IRB-20; approved September 2, 2022). This protocol is registered with ClinicalTrials.gov (Registry number: NCT05656352, Registration date: December 19, 2022, URL of the trial in the registry database:
https://clinicaltrials.gov/ct2/show/NCT05656352).

### Study sample

**
*Recruitment of participants*
**

A sample of 900 pregnant women from each site will be selected from the PRISMA study primary cohort, for a total of 2700 participants. Participants may be recruited sequentially through household-based or facility-based pregnancy surveillance (e.g., the first 900 women enrolled in PRISMA will also be included in this study from the date of protocol approval per site).

**
*Eligibility criteria*
**

Any participant that is eligible for the PRISMA study is also considered eligible for this study. However, research staff may exclude women from the study, based on the presence of injury, deformity, tattoo, or birthmark that interferes with Masimo sensor placement or performance or a finger size that does not appropriately fit the device. Presence of henna, nail polish or long nails is not an exclusion criterion, but staff will record information about these factors as they might interfere with the Masimo device performance.

**
*Consent*
**

PRISMA MNH uses a multiphase process to recruit women through pregnancy surveillance. Consent or assent will be obtained from pregnant women after a pre-screening process to determine eligibility in the PRISMA MNH study.

**
*Study status*
**

The parent PRISMA MNH study began recruiting and enrolling pregnant women on 22 September 2022 (Pakistan), 23 November 2022 (Kenya), and 15 December 2022 (Zambia). The study is planned to complete enrollment at the end of 2025. 

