### Aim and objectives

The primary aim of this study is to evaluate whether total hemoglobin measures using the Masimo SpHb continuous non-invasive monitoring device are accurate as compared to gold standard CBC laboratory tests using peripheral venous blood samples. To achieve this aim, three statistical objectives were identified:

1.To estimate the level of deviation and agreement between SpHb and CBC values longitudinally.2.To calculate the level of agreement between SpHb and CBC values among binary (healthy versus anemic) and ordinal (mild, moderate, severe anemia versus normal) measures longitudinally.3.To describe sociodemographic and clinical factors affecting the difference between SpHb and CBC values.

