### Data quality control

**
*Equipment standardization and calibration*
**

All laboratory measurements will be conducted according to standardized operating procedures (SOPs) internally developed for the parent study. Specifically, research staff and laboratory technicians will follow exactly the Laboratory SOP, Maternal Clinical SOP, Infant Clinical SOP, and the Anthropometry Quality Assurance and Quality Control (QAQC) SOP. These SOPs describe in detail the required equipment (including test kit models) and instructions for equipment calibration and maintenance, biological specimen collection, specimen processing, sample management, and results reporting. Participating laboratories will also perform scheduled quality checks and were required to enroll in the United Kingdom National External Quality Assessment Scheme (UK NEQAS) for hematology. In addition, for the purposes of this substudy protocol, the five-part differential hemoglobin analyzer and Masimo device will be routinely calibrated according to the company's guidelines. Each Masimo device user will receive training from the company, and we will maintain a daily use log as outlined in the SOP.

**
*Corrective action*
**

SpHb: Cases with reference errors (difference between the SpHb and CBC measurements greater than 0.5 g/dL, missing paired CBC reading), user errors (incorrect device setting) and problematic signal quality checks (low signal stability, low performance improvement quality (low perfusion), low SpHb confidence (ambient light interference) - indicated as spot-check monitoring results on the instrument) will be recorded to quantify the percent of cases with failure using lab-designated SOPs.

If there are errors related to CBC, samples should be re-run in case of any errors. If errors persist, lab designated SOPs (such as a daily QC log) will be used to document the errors and appropriate personnel will be notified. Issues related to blood draw (e.g., hemolysis) will be documented for corrective actions, but more blood will not be drawn.

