Statistical analysis will be performed using both per-protocol (PP) (excluding outliers and errors) (n<900) and intention-to-treat (ITT) (including outliers and errors) (n=900) analyses. Different from randomized clinical trials where PP and ITT refer to the exclusion or inclusion of data points when participants do not comply to their assigned treatments, here PP and ITT refer to the exclusion or inclusion of data points when the technician didn’t follow the protocol or user’s manual in correctly collecting blood sample or measuring hemoglobin levels, which may lead to outliers or errors.

**
*Missing data*
**

We will examine the percentage and patterns of missingness of the hemoglobin measurements. In cases where missingness is high (e.g., >10%) or cases where missing probabilities are associated with certain factors, multiple imputations (MI) will be carried out. An inclusive imputation model will be employed with all relevant risk factors and hemoglobin measurements from the same patient at different time points. MI results will be compared to the complete case analysis to test the robustness of our conclusions of missing data.

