### Objective 3: Factors affecting differences between SpHb and CBC

In order to assess factors that might affect the accuracy of SpHb, we will include the following characteristics in linear mixed models in order to assess differences between paired SpHb and CBC measurements. These variables will be collected during the enrollment visit, ANC visit, and or during the postpartum visit.

Maternal age,Anemia severity stratum,Nutritional status (e.g., iron deficiency),HIV status (Zambia and Kenya sites only),Malaria status (Kenya site only),Helminth infection status (Kenya site only),Gestational age at assessment and at first ANC visit,Technician,Time between SpHb collection and CBC collection,Participant’s early pregnancy BMI (measured at first ANC visit),Mid upper arm circumference (MUAC),Study site,Tobacco use,Estimated plasma volume (PV)
^
17
^ where Kaplan-Hakim formula
^
18
^ estimates PV as: 

PV(cPV)=(1−hematocrit)∗[a+(b∗weightinkg)]

Where,
*a = 1,530* in males and
*864* in females, and

*b = 41* in males and
*47.9* in females.

We will assess differences between these subgroups as follows:

*Candidate forms of the differences in hemoglobin levels (outcome):*

Differences (
*Δ* =
*SpHb*–
*CBC*),Absolute differences |
*Δ*|,Log(SpHb) - log(CBC) = log(SpHb/CBC).

*Comparison of the outcomes across different categories:*

Contingency tables will be constructed where the distribution of the outcome (differences) will be compared across different levels of the risk factors. For example, mean/SD/IQR of the outcome will be listed side by side for each site and p-values using mixed models comparing the distributions between different locations will be reported.

*Plot of the outcome versus risk factors:*

Lowess or kernel smoothing curves will be fitted for the relationship between the outcome and continuous risk factors such as true Hb values.

*Univariate analysis of candidate risk factors:*

One linear mixed model will be fitted for each candidate risk factor. Candidate risk factors will be tested one at a time and marginal associations between the size of measurement errors and each risk factor will be reported as change per sample SD or change w.r.t. reference level, 95% confidence interval and p-values. All effect sizes and CI can be reported in a forest plot

*Multivariate analysis of selected candidate risk factors:*

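### Henna, nail polish and long nails are recorded as possible sources of device error, but the Objective 3 covariate list leaves them out and no other analysis uses them

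*Protocol article*

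**What the plan says.** Under Study sample (Eligibility criteria), an injury, deformity, tattoo or birthmark that interferes with the sensor, or an ill-fitting finger, may lead to exclusion. Nail and skin coverings are treated differently: henna, nail polish and long nails do not exclude a woman, but "staff will record information about these factors as they might interfere with the Masimo device performance". The stated reason is possible interference with the device.

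The third objective, under Aim and objectives, is "To describe sociodemographic and clinical factors affecting the difference between SpHb and CBC values". The Objective 3 section of the analysis plan puts it more broadly, as factors that might affect SpHb accuracy, and commits to a list: "we will include the following characteristics in linear mixed models in order to assess differences between paired SpHb and CBC measurements". The list covers maternal age, anemia severity, nutritional status, HIV, malaria, helminths, gestational age, technician, time between collections, BMI, MUAC, site, tobacco use and estimated plasma volume. The summary tables, univariate models, elastic net and final mixed model that follow are described for these candidate factors.

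Separately, Data quality control (Corrective action) names "problematic signal quality checks (low signal stability, low performance improvement quality (low perfusion), low SpHb confidence (ambient light interference" among the events that "will be recorded to quantify the percent of cases with failure using lab-designated SOPs".

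**The concern.** The protocol names three things that might disturb the reading, keeps the affected women in, and collects the data. The one objective meant to explain the SpHb-CBC difference then has no place for them. Two things are at stake.

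- **An unanswered practical question.** A validation study of a finger sensor should be able to tell users whether henna, polish or long nails shift the reading. The data would be there, but no planned analysis would use them.
- **A site contrast that is hard to read.** The plan compares the SpHb-CBC difference between sites with p-values. If one of these factors shifts the reading and its prevalence differs between Zambia, Kenya and Pakistan, part of the apparent site difference belongs to that factor.

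**Working it through.** **Comparing the lists.** The plan states no figure on this point, so the core check is textual.

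| Factor | Recorded? | Stated reason or use | In Objective 3 list? |
|---|---|---|---|
| Henna | yes | may interfere with device | no |
| Nail polish | yes | may interfere with device | no |
| Long nails | yes | may interfere with device | no |
| Technician | yes | none given | yes |
| Time of SpHb and CBC collection | yes | none given | yes, as time between collections |

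None of the three factors is listed. The last two rows show that factors of the measurement process are within the scope of Objective 3. Box 1 also omits the three, but that adds little: it holds parent-study variables, and technician and timing are missing from it too.

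**What could be estimated if they were added.** Inputs from Sample size considerations: 900 women per site, 90% power, significance level 0.05 (taken as two-sided). These reproduce the plan's own figure: (1.96 + 1.28)/√900 = 3.24/30 = 0.108 SD, and the exact one-sample t-test at n = 900 and 0.108 SD gives power 0.899.

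For a yes/no factor with prevalence p among N women, one pair each, the detectable difference in mean SpHb-CBC, in SD of the differences, is

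3.24 × √[1/(Np) + 1/(N(1−p))].

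At N = 900 and p = 10%: √(1/90 + 1/810) = 0.111, and 3.24 × 0.111 = 0.36 SD. Prevalence is not in the documents, so a range is shown:

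| Assumed prevalence | One site (N = 900) | Pooled (N = 2,700) |
|---|---|---|
| 2% | 0.77 SD | 0.45 SD |
| 5% | 0.50 SD | 0.29 SD |
| 10% | 0.36 SD | 0.21 SD |
| 20% | 0.27 SD | 0.16 SD |

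The pooled column assumes that exposure is spread evenly over sites. If it sits mostly at one site and the model adjusts for site, the one-site column is the better guide.

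**How far a site contrast could move.** The shift equals the factor's effect times the difference in prevalence between two sites. Neither is in the documents. For an assumed effect of 0.5 SD:

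- prevalence difference 0.10: 0.5 × 0.10 = 0.05 SD
- prevalence difference 0.20: 0.5 × 0.20 = 0.10 SD
- prevalence difference 0.30: 0.5 × 0.30 = 0.15 SD

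For scale, a contrast of two sites of 900 can detect 3.24 × √(1/900 + 1/900) = 0.15 SD with 90% power. Only the top of this assumed range reaches that level.

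**The case against.** **The list may not be closed.** Objective 3 also plots the outcome against true hemoglobin, which is not listed in that form, and the final model allows adjustment by hand on clinical grounds. The article is condensed, and a fuller plan may exist. This lowers certainty about what the analysts will do. It does not remove the mismatch: the article contains its own analysis plan with an itemised list, and that list omits factors the same article calls possible sources of interference.

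**The objective is worded as sociodemographic and clinical.** True under Aim and objectives, but the Objective 3 section already admits technician and timing.

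**The per-protocol comparison covers it.** It does not cover the nail and skin factors. That comparison concerns "exclusion or inclusion of data points when the technician didn’t follow the protocol or user’s manual", and a correctly taken reading through henna is not such a failure.

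**The consequence is limited.** This largely stands. Objective 3 is descriptive, site-specific analyses are not affected by prevalence differences between sites, and the planned agreement estimates of Objectives 1 and 2 do not depend on this list.

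A reader might also infer that the signal-quality flags are neglected in the same way, or that flagged pairs are dropped from the per-protocol set. The documents do not support either. The interference wording covers only henna, polish and nails. The flags have a stated use of their own, counting failures. The per-protocol set leaves out outliers and errors, but no sentence says that a flagged reading is one. Flags are also read-outs of the measurement itself and may lie on the path from a woman's characteristics to the SpHb error, so their absence from a multivariable model is defensible.

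**Conclusion.** The point holds for henna, nail polish and long nails. They are recorded because they might disturb the device, they are absent from the Objective 3 list, and no other described analysis uses them. As written, their effect on the SpHb-CBC difference would not be estimated, and a site contrast could absorb it if prevalence differs by site.

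The size of that effect is unknown. The detectable differences above rest on assumed prevalence, a two-sided test at 0.05 and one pair per woman. They show that moderate effects could be estimated unless the factors are rare. They do not show that such effects exist. It would go too far to say that the site comparison is biased, or that the primary agreement results are compromised. This is a worthwhile correction to a secondary objective, not a threat to the study's main conclusion.

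**What to change.** Add henna, nail polish and long nails to the Objective 3 candidate list as yes/no factors. Fit each in the univariate mixed models and carry them into the multivariable mixed model, using all pairs (the set that the plan calls ITT). Code them by visit if they are recorded at each visit, and otherwise as recorded.

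The signal-quality flags can be described in univariate comparisons of the SpHb-CBC difference. They should not be forced into the multivariable model, because they may mediate the participant effects that Objective 3 sets out to describe.

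The cost is small but not nil. It is a few more model terms, plus confirmation of how often the three factors are recorded: the protocol mentions the recording under eligibility and does not say that it is repeated at each of the five time points. If it is not, visit-level coding would need a change in data collection.

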### Data collection

**
*Methods of measurement*
**

At enrollment, all participants selected for inclusion in the study will undergo Masimo Total Hemoglobin (SpHb) at the same time that peripheral venous blood is drawn for hemoglobin testing via CBC (gold standard method) as part of the parent study (
Table 1). At all subsequent study visits, participants will receive hemoglobin testing using both CBC and the Masimo device (SpHb). The SpHb measurement and blood draw for CBC should be done concurrently, or as close in time as is possible. Time of SpHb measurement and CBC collection and analysis will be recorded. Additionally, the IDs of the technicians collecting SpHb measurement and of technicians analyzing CBC (not the ones collecting blood specimens for CBC analysis) on the hematology analyzer will be recorded.

**Table 1. T1:** Description of hemoglobin measurement by method.

Measurement	Biological sample	Method	Order of test
SpHb	N/A	Masimo Rad-67 ^®^ Pulse CO-Oximeter and rainbow ^®^ sensors	First (with vital signs)
CBC	Venous blood in EDTA tubes. To be analyzed within 6 hours of collection or stored at 2 to 8C and analyzed within 24 hours.	Beckman Coulter DxH520 five-part differential hematology analyzer (in Pakistan) or Sysmex XN-1000™ Hematology Analyzer five-part differential (in Zambia) or Beckman Coulter, Ac.T 5 Diff CP (Cap Pierce) (in Kenya)	Second (after SpHb)

Additional variables collected or calculated as part of the PRISMA MNH parent study that will be used in this substudy analysis can be found in
Box 1, below. All data is collected by trained research staff using designated collection tools that correspond to scheduled study visits conducted either at a study facility or at the participants’ home.

Box 1. List of maternal characteristics•     Maternal age,•     Anemia severity stratum,•     Nutritional status (e.g., iron deficiency),•     HIV status (Zambia and Kenya sites only),•     Malaria status (Kenya site only),•     Helminth infection status (Kenya site only),•     Gestational age at assessment and at first ANC visit,•     Participant’s early pregnancy BMI (measured at first ANC visit),•     Mid upper arm circumference (MUAC),•     Study site,•     Tobacco use,•     Estimated plasma volume (PV).

Software used in the parent study are detailed in
Figure 2. Three different site-specific servers (Kenya: ASP.net and SQL; Pakistan: OpenSRP; Zambia: Teleform) will be used for data collection. After the internal quality checks conducted by site data managers, de-identified data will be uploaded to the secure Bill & Melinda Gates Foundation (BMGF) server Synapse. Data will then be transferred for storage and analysis to the PRISMA Amazon Web Services (AWS) Server at the George Washington University (coordination site).

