### Sample size considerations

**
*Total sample size*
**

The total sample size of 900 per study site will give 90% power for site-specific analyses to detect a systematic shift (defined as mean difference between each pair of SpHb and CBC divided by the standard deviation of all paired differences) of size 0.108 between the mean of SpHb measurements and the mean of CBC measurements. That is, if the SpHb system shifts from the reference CBC measurements by 10.8% of the SD of the mean difference, the probability that we will detect such a systematic shift using one sample t-test with significance level 0.05 is 90%. The total sample size of 900 will also give 80% power to detect a systematic shift of size 0.093*SD between the mean of SpHb measurements and the mean of CBC measurements. The SD can be calculated in the same way as those in the Bland Altman plots. However, 900 is a very conservative estimate of the sample size and would be sufficient to analyze the three sites independently. Based on our pilot data from Kenya and Pakistan, the mean difference between SpHb and CBC is approximately 0.8 times its SD; even a sample size as small as 19 pairs would provide 90% power using one-sample t-test.

In detecting the extreme differences (i.e. large absolute value) between the SpHb and CBC measures on the same sample, the sample size of 900 will give 99.99% probability to detect the top 1% largest values in the distribution of all differences. It will also give 98.90% probability to detect the top 0.5% largest values in the distribution of all differences, and 93.31%, 83.50%, 59.36% probability to detect the top 0.3%, 0.2%, 0.1% largest values in the distribution of all differences, respectively. With three repeated measures from each of the 900 participants, the listed probabilities are conservative estimates of chances in catching extreme values.

**
*Strata sample size*
**

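### Each country has its own CBC analyzer model, so the Objective 3 site effect on SpHb minus CBC cannot be separated from a calibration offset between reference analyzers

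*Protocol article*

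**What the plan says.** **Reference instruments.** Table 1 (Data collection) names one analyzer model per country: "Beckman Coulter DxH520 five-part differential hematology analyzer (in Pakistan) or Sysmex XN-1000™ Hematology Analyzer five-part differential (in Zambia") and "Beckman Coulter, Ac.T 5 Diff CP (Cap Pierce) (in Kenya"). No model appears in more than one country.

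**Use of site.** Objective 3 opens: "In order to assess factors that might affect the accuracy of SpHb, we will include the following characteristics in linear mixed models". Site is on the list ("Mid upper arm circumference (MUAC),Study site,Tobacco use"); analyzer is not. The outcome is SpHb minus CBC, or its absolute or log form. Site is also the article's worked example of a between-group comparison: "p-values using mixed models comparing the distributions between different locations will be reported".

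**Controls on the reference.** The Data quality control section describes common laboratory procedures and scheduled quality checks. It says the laboratories "were required to enroll in the United Kingdom National External Quality Assessment Scheme (UK NEQAS) for hematology", and that "the five-part differential hemoglobin analyzer and Masimo device will be routinely calibrated according to the company's guidelines". It describes no exchange of split samples between the laboratories, and states no use of the quality scheme results in the analysis.

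**Sample size.** "The total sample size of 900 per study site will give 90% power for site-specific analyses to detect a systematic shift".

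**The concern.** The outcome is a difference between two instruments. The article names the same non-invasive device for all sites, but the reference model changes with the country. If one country's analyzer reads slightly high, SpHb minus CBC is lower there by that amount, even if the Masimo device performs identically everywhere. The planned model would show this as a site effect, and the stated purpose of the analysis invites the reader to take it as a factor affecting SpHb accuracy.

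What is at stake is the interpretation of one Objective 3 result: a conclusion that the device works better or worse in one country could in fact describe that country's reference instrument.

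**Working it through.** **1. Identifiability.** For site *k*, let *s_k* be the mean error of SpHb and *a_k* the mean error of that site's analyzer, both relative to true hemoglobin. The mean of SpHb minus CBC at site *k* is *s_k* − *a_k*. The contrast of sites *k* and *l* is

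(*s_k* − *s_l*) − (*a_k* − *a_l*).

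Each site has only its own analyzer model, so the data determine this combination and neither part of it. As a check, a design matrix with an intercept, two site indicators and two analyzer indicators has 5 columns and rank 3. The analyzer indicators add nothing beyond site, so neither covariate adjustment nor more participants can separate the two.

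**2. The article's own power figure.** Inputs from Sample size considerations: n = 900 per site, significance level 0.05, one-sample t-test.

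- 90% power: (1.960 + 1.282) / √900 = 3.242 / 30 = 0.108 SD, as stated.
- 80% power: (1.960 + 0.842) / √900 = 2.802 / 30 = 0.093 SD, as stated.
- The exact two-sided t calculation gives 89.9% at 0.108 SD and 79.6% at 0.093 SD. The figures reproduce.

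**3. The same method for two sites.** With 900 against 900 and one pair per woman:

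- 90% power: 3.242 × √(2/900) = 3.242 × 0.0471 = 0.153 SD.
- 80% power: 2.802 × 0.0471 = 0.132 SD.

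The article does not give the SD of paired differences in g/dL. For assumed values, the 90% threshold is:

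- SD 0.8: 0.153 × 0.8 = 0.12 g/dL
- SD 1.0: 0.153 × 1.0 = 0.15 g/dL
- SD 1.3: 0.153 × 1.3 = 0.20 g/dL

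**4. Chance that an offset alone gives p < 0.05.** This supposes no true difference between sites in SpHb performance. Offset and SD are both assumed, for illustration. Power ≈ Φ(offset / (SD × 0.0471) − 1.960).

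| Assumed offset | SD 0.8 | SD 1.0 | SD 1.2 | SD 1.5 |
|---|---|---|---|---|
| 0.1 g/dL | 75.5% | 56.4% | 42.4% | 29.3% |
| 0.2 g/dL | about 100% | 98.9% | 94.2% | 80.7% |
| 0.3 g/dL | about 100% | about 100% | about 100% | 98.9% |

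Example: offset 0.2, SD 1.0 gives 0.2 / 0.0471 = 4.24; 4.24 − 1.96 = 2.28; Φ(2.28) = 98.9%.

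**5. What a fixed offset leaves intact.** For the signed difference, a constant *a_k* cancels in any comparison inside one site, between women or over time. It shifts that site's estimated bias and both limits of agreement by the same amount, so the width of the limits does not change.

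**The case against.** **Attribution.** The Aim and objectives section frames Objective 3 as describing factors related to the difference between the two measurements, and site is a composite term in any multi-country study. A site difference can be read as a difference in agreement with each site's own reference. That reading is legitimate, and it is the one recommended below. But the opening of the Objective 3 analysis speaks of SpHb accuracy, so the text as it stands points to the other reading.

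**Quality controls.** Common procedures, manufacturer calibration and the external scheme may keep offsets small. This stands as mitigation. It does not make the contrast identifiable: calibrating each analyzer to its own company's guidelines is not cross-calibration between models, and no use of the scheme's results to bound or remove an offset is stated.

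**Magnitude.** No offset is documented, and the probabilities in the table depend on assumed values. This stands in full. The 0.153 SD threshold is also only about one fifth of the pilot mean difference of roughly 0.8 SD (0.153 / 0.8 = 0.19), so an offset of that size would not overturn the main question of agreement.

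**Stronger readings that the documents do not support.**
- *A significant site effect is highly likely, or will be due to the analyzers.* A large sample does not create an effect, and nothing in the article shows that an offset exists.
- *Quality scheme results will never be used in the analysis.* The article is silent, and a condensed article may leave this to the full plan.
- *Pooled bias and limits of agreement will be contaminated.* No pooled Bland–Altman analysis is specified. The analysis sets are given at the per-site number, and the sample size section supports separate analysis of the three sites.

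**Conclusion.** The point holds as a matter of identifiability. With a different reference analyzer model in each country, the site effect on SpHb minus CBC is completely aliased with any calibration offset between analyzers, and it cannot be reported as an effect on SpHb accuracy alone. This rests on Table 1 and the Objective 3 text and needs no assumption about the size of an offset.

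The practical weight does depend on assumptions. With one pair per woman and an SD of 0.8 to 1.3 g/dL, an offset of 0.12 to 0.20 g/dL between two analyzers, if present, would reach significance with 90% probability. An offset of 0.1 g/dL would do so with probability 29% to 76% for an SD of 1.5 down to 0.8 g/dL.

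A reader might infer that Objective 3 as a whole, or the study, is uninterpretable. It is not: within-site contrasts of the signed difference are unaffected by a fixed offset, and site-specific agreement with the local reference remains a valid result. The defect lies in the between-site contrast, and it is worth correcting before analysis.

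**What to change.** 1. In Objective 3, define and report the term as site/reference analyzer, and state that its p-value is not evidence of a factor affecting SpHb accuracy.
2. Keep bias and limits of agreement site-specific, which the sample size section already supports.
3. Where the existing external quality scheme returns give a usable hemoglobin bias for each laboratory, add a sensitivity analysis of the site contrasts, and of any pooled bias or limits, with that bias removed and its uncertainty carried through. If the returns do not give such a figure, say so and leave the contrast unattributed. The article does not say what the returns contain, so this step is conditional.

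The cost is a more cautious conclusion about site, retrieval of existing quality reports and a little extra analysis. No new participants or samples are needed.
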